### Secondary objectives related to the intervention

*Objective 1*: To report the difference in the proportion of people adopting regular exercise habits, cessation of smoking, and adopting healthy dietary habits between control and intervention groups

*Objective 2*: To report the general health literacy among the total study participants

*Objective 3*: To report the willingness to receive and pay for a text message system for lifestyle modification

*Objective 4*: To report the perceived barriers and enablers in participating and adopting lifestyle modifications to manage blood pressure

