### Sequence generation

Statistically, a simple random sampling technique (an unbiased coin toss) will be used to select the intervention group. The cluster is the unit of randomness but not the individual participants within clusters. However, within a cluster, we will aim to recruit participants with a male to female ratio equivalent. In that case, the restriction is to recruit one male after recruiting one female participant to make the sex ratio equivalent. Therefore, no random sequence will be generated. However, the complete list of potential percipients with hypertension is available from the previous cross-sectional study [15]. The study location, participants, and their socioeconomic condition can be accessed from the Narail district statistics [40].

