### Statistical analyses

Although the intervention will be conducted as clusters, data will be collected as individuals within clusters and the effect of the intervention will be measured based on individual’s data. Since the randomization is based on clusters, there might occur differences in baseline characteristics of participants. The baseline characteristics for the intervention and the control group will be examined using the chi-square test or Fisher’s exact test for categorical variables and the two-sample *t-*test or Mann-Whitney U test for continuous variables depending on the distributions of the data.

The effect size will be the mean difference in the primary outcome. The comparison will be made between differences for control and intervention groups after the follow-up. More specifically, it could be shown as the difference between DifCon and DifInt. DifCon equals the difference between baseline and follow-up for the control group, and DifInt equals the difference between baseline and follow-up for the intervention group. Such comparison will give the actual effect size due to the intervention. Generalized linear model (GLM) will be used for analytical purpose, and the models will be adjusted for factors which are different between control and intervention groups at baseline. For the secondary outcomes (motivation to smoking cessation, change in dietary patterns, and physical activity), chi-square tests will be used to detect any associations in the outcome variables across gender, age categories, level of education, and socioeconomic status. The difference in proportion with 95% confidence interval between control and intervention groups will be computed using the test of proportion, and odds ratios (OR) with 95% confidence interval will be computed using logistic regression techniques. The models will be adjusted for covariates as appropriate.

Rasch analysis using RUMM30 software will be used to investigate the psychometric properties of the Health Literacy tool and to compute the overall score from the 12-item HLS-Q12 tool. Individual item, as well as the overall score from all items combined, will be compared for gender, age group, level of education, occupation, and SES using chi-square, *t*-tests, or ANOVA as it is appropriate.

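### The chi-square tests of behaviour outcomes by demographic factor leave out trial arm, so at follow-up a programme effect can appear as an association with age, education or socioeconomic status (minor)

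*Protocol article*

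**What the plan says.** The Statistical analyses section names three secondary outcomes (motivation to stop smoking, change in diet, physical activity) and says that "chi-square tests will be used to detect any associations in the outcome variables across gender, age categories, level of education, and socioeconomic status". The test, the outcomes and the factors are fixed. Arm, stratification and time point are not mentioned.

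The following sentences deal with the arms separately: "The difference in proportion with 95% confidence interval between control and intervention groups will be computed using the test of proportion". For the regression part, the plan states that "odds ratios (OR) with 95% confidence interval will be computed using logistic regression techniques". On adjustment of these models it adds: "The models will be adjusted for covariates as appropriate". This between-arm comparison is what secondary objective 1 asks for: "To report the difference in the proportion of people adopting regular exercise habits, cessation of smoking, and adopting healthy dietary habits between control and intervention" arms.

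Two further statements matter. The same section concedes: "Since the randomization is based on clusters, there might occur differences in baseline characteristics of participants". The Sequence generation section says that "within a cluster, we will aim to recruit participants with a male to female ratio equivalent".

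Table 1 schedules the smoking, diet and physical activity questionnaires both at baseline and at follow-up.

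**The concern.** Where the Statistical analyses section means a comparison by arm, it says so. The sentence on demographic factors does not, so its most natural reading is one table per factor over all participants. A change in diet needs a follow-up value, so at least part of this testing uses data collected after the programme has acted on one arm only.

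In such a table, arm is a potential confounder. If the programme works and, say, better-educated participants are more common in the intervention block, education will appear related to adoption even when it is unrelated within either arm. Allocation is one coin toss between two blocks of villages, so randomization cannot be relied on to balance these factors, and the plan itself allows for imbalance. It adjusts the primary blood pressure model for factors that differ at baseline, but a plain chi-square test cannot adjust for anything.

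At stake is the interpretation of the demographic findings. The Discussion hopes that the results will inform wider programmes. A statement that adoption differs by education could be read as guidance on whom to target, when it may only reflect which villages received the programme.

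**Working it through.** The protocol gives no figure for these tests, so there is none to reproduce.

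**Inputs from the protocol.** 106 evaluable and 150 recruited participants per arm (Sample size).

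**Assumptions (not in the protocol).** Adoption at follow-up is 30% in control and 50% in intervention. The factor is binary and has no effect within either arm. It is held by a share q_T of the intervention block and q_C of the control block. The test is two-sided at 5%. Participants are independent, so village clustering is ignored.

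**Step 1: the false gap.** With shares of 60% and 40%:
- factor present: 0.6 × 0.50 + 0.4 × 0.30 = 0.42
- factor absent: 0.4 × 0.50 + 0.6 × 0.30 = 0.38
- gap = 0.04, which equals (0.50 − 0.30) × (0.60 − 0.40)

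With shares of 70% and 30% the gap is 0.20 × 0.40 = 0.08. With equal shares it is zero.

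**Step 2: rejection rate at 106 per arm, 60/40 split.** Each factor group has 63.6 + 42.4 = 106 people.
- Standard error used by the test: √(0.40 × 0.60 × 2/106) = 0.0673, so the critical gap is 1.96 × 0.0673 = 0.1319.
- Actual standard error: √[(63.6 × 0.25 + 42.4 × 0.21 + 42.4 × 0.25 + 63.6 × 0.21)/106²] = 0.0659.
- Upper tail: 1 − Φ((0.1319 − 0.04)/0.0659) = 1 − Φ(1.39) ≈ 0.082.
- Lower tail: Φ((−0.1319 − 0.04)/0.0659) = Φ(−2.61) ≈ 0.005.
- Total ≈ 8.6%.

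The same formula at 150 per arm gives 10.4%.

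**Step 3: simulation, 20,000 trials per row.**

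| Adoption, control vs intervention | Factor share by block | Plain chi-square, 106 per arm | Plain chi-square, 150 per arm |
|---|---|---|---|
| 30% vs 50% | 60/40 | 9.3% | 10.9% |
| 30% vs 50% | 70/30 | 22.3% | 29.5% |
| 30% vs 60% | 60/40 | 13.8% | 18.4% |
| 30% vs 60% | 70/30 | 42.5% | 55.7% |

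With equal shares the plain test stays near 5%. The Mantel-Haenszel test stratified by arm stays at about 5% in every scenario.

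**Step 4: smaller imbalance or effect.** By the Step 2 formula at 150 per arm, a 55/45 split with 30% vs 50% adoption gives 5.9%. A 60/40 split with 30% vs 40% adoption gives 6.4%. The distortion therefore needs both a clear imbalance and a sizeable programme effect.

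**The case against.** The case against giving this weight is substantial, and most of it stands.

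- **The text never says that the arms are pooled.** True. That is an inference from a sentence that omits arm. It is the natural reading, but not a stated fact.
- **The questionnaires are also given at baseline, and Table 1 plans for baseline data to be analysed before follow-up ends.** Randomization comes after baseline collection, so an all-participant chi-square test there is free of any programme effect. This stands. The point applies only to follow-up and change outcomes, and change in diet must be one of them.
- **The programme effect is judged elsewhere.** This also stands. The difference in proportions and the logistic regression compare the arms directly.
- **Imbalance is only a possibility.** The plan says that differences might occur, and the Cluster randomization section considers similar risk factors highly likely. Sex is meant to be balanced within clusters, so the confounding concerns mainly age, education and socioeconomic status.

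A reader might go further and infer that a programme working in only one subgroup would be missed. The documents do not support that as a fault. No objective asks about subgroup effects, and interaction tests are commonly left to the analysis plan. The planned arm comparison can also still react. If the programme raised adoption in women from 30% to 50% while men stayed at 40% in both arms (150 per arm, assumed rates), the plain test by sex would reject in 4.7% of trials, but the arm comparison in 43%, the same as an arm-by-sex interaction test. It would not show that the effect lies in women. Only contrived cases, such as opposite effects of +20 and −20 points, escape both planned tests (4.2% and 4.8%, against 97% for the interaction test).

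What remains is that the stated method, applied to follow-up data, cannot separate a demographic association from an arm effect.

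**Conclusion.** The point holds in a limited form and is minor. As written, the demographic tests omit arm. Applied to follow-up or change outcomes over all participants, they can report associations with age, education or socioeconomic status that are only the programme effect combined with imbalance between the village blocks. Under assumed adoption of 30% vs 50% and a 60/40 split, rejection is about 9 to 11% instead of 5%. It is higher under stronger imbalance or a larger effect, and there is no distortion when the factor is balanced. Adoption rates and shares are assumptions, and clustering is ignored.

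Only the reported demographic associations are affected. Neither the blood pressure result nor the between-arm estimates for the behaviour outcomes depend on these tests.

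**What to change.** State the time point of the demographic tests. For follow-up and change outcomes, either stratify them by arm (Cochran-Mantel-Haenszel) or add arm, with the demographic factor, to the logistic models already planned. Keep plain chi-square tests for baseline data. An arm-by-factor term is optional and should be labelled exploratory, since no subgroup effect is an objective.

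The cost is one sentence in the Statistical analyses section and one stratification variable or model term. Arm is known for every participant, so no new data are needed and the sample size does not change.

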### Cluster randomization

Randomization will be performed after the recruitment of all participants and the baseline data collection. The entire 18 villages will be divided into two clusters: one cluster is with nine villages, about 50% of the study location, and the other cluster is with the remaining nine villages. The clusters are the unit of randomization. Each cluster has 150 participants; 10 to 20 participants are from each village based on the village size within a cluster. The intervention and the control group will not be divided into mutually exclusive groups based on risk factors for high blood pressure. This is because (i) this is highly likely that both clusters will have similar risk factors for high blood pressure and (ii) the intervention will be more practical given the nature of the intervention where participants will work as a team formed in different villages.

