#### Secondary outcomes

(i)Psychometric properties of the HLS-EU-Q12 [36] questionnaire which is a 12-item questionnaire and was developed and evaluated in European countries for measuring health literacy. There are no validated tools for measuring health literacy in Bangladesh where HLS-EU-Q12 could potentially be used. However, it is unknown whether all items are appropriate as in Bangladesh. Therefore, assessing the reliability and validity of the HLS-EU-Q12 tool is a secondary outcome. Psychometric properties of the HLS-EU-Q12 [36] will be assessed at baseline only.(ii)Level of health literacy at baseline. After assessing the psychometric properties, we may come up with all 12 items or remove one or two items. Based on the validated tool, we will estimate the health literacy among the participants with high blood pressure. The outcome measure will be the proportion of people who have different levels of health literacy such as above or below average. The level of health literacy will be estimated at baseline only.(iii)The proportion of the smoker who smoked at baseline and at 6 months, and the proportion of smokers who intend to quit or reduce smoking within 1 month or 3 months at baseline and achievement after the intervention. Time frame: (1) baseline and (2) immediately after the intervention (6 months).(iv)The proportion of people who take regular physical exercise and who intend to take part in physical activities. To measure this outcome, the GPAQ [42] tool will be used. The difference in the proportion of participants who take part in regular exercise was measured at baseline and at follow-up. Time frame: (1) baseline and (2) immediately after the intervention (6 months).(v)The proportion of people who use their own mobile phone, can read SMS, and have the intention to receive and pay for SMS for health information. Time frame: baseline only.(vi)Perception of and practice in raw salt consumption. The outcome measure is the proportion. Tool: a modified version of Q-MAT [43]. Time frame: (1) baseline and (2) immediately after the intervention (6 months).(vii)Perceived barriers and enablers in participating and adopting lifestyle modifications to manage blood pressure. This is descriptive information. The software NVivo will be used to investigate if there are any common themes of barriers which could intervene. Time frame: immediately after the intervention (6 months).

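### For regular exercise and raw-salt practice, the planned risk difference comes from an unadjusted test of proportion with no stated input; if that input is 6-month prevalence, it does not measure adoption when the two village blocks differ at baseline

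*Protocol article*

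**What the plan says.** Secondary objective 1 of the protocol article is "To report the difference in the proportion of people adopting regular exercise habits, cessation of smoking, and adopting healthy dietary habits between control and intervention" (the two arms). Adopting a habit is a change of status from where the participant began.

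The secondary outcomes are worded as proportions at each visit. For exercise (outcome iv): "The difference in the proportion of participants who take part in regular exercise was measured at baseline and at follow-up". For salt (outcome vi): "Perception of and practice in raw salt consumption. The outcome measure is the proportion", with baseline and 6 months as the time points. Table 1 schedules the physical activity and dietary questionnaires at both visits.

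Under Statistical analyses, the between-arm comparison of the secondary outcomes has two parts. The first is a risk difference: "The difference in proportion with 95% confidence interval between control and intervention groups will be computed using the test of proportion". The second is a model: "odds ratios (OR) with 95% confidence interval will be computed using logistic regression techniques. The models will be adjusted for covariates as appropriate".

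The same section accepts that the arms may not start level: "Since the randomization is based on clusters, there might occur differences in baseline characteristics of participants". For blood pressure it responds by comparing the baseline-to-follow-up change in one arm with the change in the other. No such step is described for the proportions.

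Allocation explains why a gap is plausible: "The entire 18 villages will be divided into two clusters: one cluster is with nine villages", the other holds the remaining nine, and one coin toss decides which block receives the intervention.

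**The concern.** A two-sample test of proportion uses one yes/no value per participant. If that value is the habit at 6 months, the null hypothesis is equal prevalence at 6 months. This coincides with equal adoption only if the two arms had the same prevalence at baseline.

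Suppose they did not, and the intervention does nothing. The block that began with more exercisers, or fewer raw-salt users, will tend to finish that way, and the comparison can be read as a programme effect. If the intervention block began behind, a real gain in adoption can be hidden. Even with level baselines, ignoring a strong predictor of the 6-month value costs power.

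These outcomes are secondary, but they are the trial's evidence on whether a lifestyle programme changed lifestyle.

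**Working it through.** The plan gives no figure for these outcomes, so there is none to reproduce. What follows sizes the problem under the prevalence reading.

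**Inputs from the document.** The sample-size section gives 106 per arm for analysis, 150 per arm recruited and about 40% loss. Taken literally, that loss leaves 150 × 0.6 = 90 per arm. The 95% confidence interval implies a two-sided 5% test.

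**Inputs assumed.** The document gives no baseline prevalence, gap, continuation rate or uptake rate. I take control baseline prevalence 40%; 80% of those with the habit continue and 15% of those without it start, equally in both arms (no effect); intervention baseline 0 to 20 points higher; participants independent. For raw salt the habit is avoiding it.

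**Step 1: expected 6-month prevalence.** With baseline prevalence b, the prevalence is 0.80b + 0.15(1 − b) = 0.15 + 0.65b. Control: 0.15 + 0.65 × 0.40 = 0.41. Thus 65% of any baseline gap persists to 6 months with no intervention effect.

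**Step 2: one case by hand.** For a 10-point gap the intervention arm reaches 0.15 + 0.65 × 0.50 = 0.475. The difference is 0.065 and the mean proportion 0.4425. At 106 per arm the standard error is √(2 × 0.4425 × 0.5575 / 106) = 0.0682, so the expected z is 0.065 / 0.0682 = 0.95. The chance that |z| exceeds 1.96 is about 16% by normal approximation. Summing exact binomial probabilities for the pooled z-test gives 15.1%.

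**Step 3: all gaps.** Unadjusted columns are exact binomial sums. The last column is a simulated Mantel-Haenszel test stratified by baseline status.

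| Baseline gap (points) | 90 per arm | 106 per arm | 150 per arm | Stratified, any n |
|---|---|---|---|---|
| 0 | 5.1% | 4.9% | 5.3% | about 5% |
| 5 | 7.2% | 7.3% | 9.3% | about 5% |
| 10 | 13.7% | 15.1% | 21.7% | about 5% |
| 15 | 24.8% | 28.5% | 41.4% | about 5% |
| 20 | 39.9% | 46.2% | 63.8% | about 5% |

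Separate simulations of 20,000 trials per scenario agree within about one percentage point; at 106 per arm one gave 7.6%, 14.8%, 28.6% and 45.9% for gaps of 5 to 20 points.

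**Step 4: sensitivity to the assumed rates, 106 per arm.** If 70% continue and 25% start, a 10-point gap gives about 9% and a 15-point gap 16%. If 90% continue and 10% start, the figures are about 21% and 41%.

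**Step 5: power, 106 per arm, uptake 15% in control and 30% in intervention.** With level baselines: 25% unadjusted and about 35% stratified. With the intervention arm 10 points lower at baseline: about 9% and 40%.

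**Step 6: limit of the remedy.** The stratified 5% holds only because Steps 1 to 4 give both blocks the same start and continue rates. If uptake were 15% in one block and 30% in the other for purely local reasons, the stratified test would reject as often as in Step 5, about 35% with level baselines, with no intervention effect.

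**The case against.** The strongest reply is that the plan never says 6-month prevalence is tested. Objective 1 speaks of adoption, and the statistical section lists change in dietary patterns among the secondary outcomes. A two-sample test of the proportion who adopted would be sound and would use baseline status by construction. This stands: a reader might infer that the plan has fixed a test of the wrong hypothesis, and the text does not support that. It leaves the input open. But outcomes (iv) and (vi) are worded as proportions at each visit, and no adoption denominator (those without the habit at baseline) is defined.

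Second, adjusted odds ratios are planned, and naming covariates is commonly left to a statistical analysis plan, which is not shown. This also stands in part. Baseline status may already be intended for the logistic model, and its absence from a condensed article is not itself a fault. The risk difference and its interval, however, come from a test that the article names, and covariate adjustment of a model does not reach them.

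Third, a systematic gap is a product of the two-block design. With individual randomisation, chance gaps are covered by the 5% level, as the zero-gap row shows. That is right. It would overstate the point to call it independent of the clustering, or to say that adjustment restores a valid 5% test. Ignoring each person's baseline status is still a separate choice, and one that analysis can improve.

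Finally, every rate is assumed, and at a 5-point gap the inflation is modest (7% to 9%). That is so, and the lost power with level baselines is an inefficiency, not an error.

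**Conclusion.** The point holds in conditional form. For regular exercise and raw-salt practice, the plan names an unadjusted comparison for the risk difference and does not state what enters it. If 6-month prevalence enters, the comparison does not answer the adoption objective when the blocks differ at baseline, and it loses precision when they do not. The plan anticipates such differences and allows for them explicitly in blood pressure only.

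The direction of the bias needs only that the habit tends to persist. Its size depends on the assumed 40% prevalence, 80% continuation, 15% uptake and independent participants: at 106 per arm, false rejection of about 7–8%, 15%, 28% and 46% for gaps of 5, 10, 15 and 20 points, and at 90 per arm about 7%, 14%, 25% and 40%. The document does not show that any such gap exists.

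Conditioning on baseline status removes only the part of the block difference that baseline status carries. It cures neither having one randomised cluster per arm nor blocks that differ in uptake for local reasons. This is a worthwhile improvement to a secondary analysis; it does not bear on the blood pressure result.

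**What to change.** For outcomes (iv) and (vi, practice), state the quantity compared and replace the unadjusted test of proportion as the main between-arm analysis:

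- Fit a logistic model for the 6-month habit with arm and the participant's own baseline status for that habit. Fix the baseline term in advance; do not make it depend on a test of baseline differences.
- Report the odds ratio and the standardised risk difference with 95% CI. The latter is the mean predicted probability over all analysed participants with arm set to intervention, minus the mean with arm set to control.
- Also report, by arm, adoption among participants without the habit at baseline.
- Keep the crude proportions at each visit as description, and define the habit identically at both visits.
- Say in the text that this adjustment does not address the single randomised cluster per arm.

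The cost is wording only, because Table 1 already collects both questionnaires at baseline and follow-up. The adoption proportion will have a wider interval because fewer participants contribute: under the assumed 40% baseline prevalence, about 0.6 × 106 ≈ 64 per arm.
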